## Background

Prostate cancer is the most common cancer in the United Kingdom, affecting one in eight men and causing the death of over 11 500 men per year [1]. Specifically, in 2020, the worldwide prostate cancer incidence, mortality and 5‐year prevalence were 14.1%, 6.8% and 20%, respectively [2].

Robot‐assisted radical prostatectomy (RARP) is the standard surgical approach to treat prostate cancer. Cancer extending beyond the prostate capsule increases the risk of positive surgical margins (PSMs), which are independent predictors of prostate cancer and biochemical recurrence after RARP [3]. RARP requires a trade‐off between performing a wider resection in order to achieve low PSM rates (11%–37% on average [4, 5]), and performing a narrower resection to preserve structures that determine functional outcomes, such as incontinence and potency, which affect patients’ quality of life [6]. Urinary incontinence remains one of the most troublesome postoperative complications, with aetiology that is complex, multifactorial, and affected by surgical technique, surgeon's skill and patient characteristics [7]. Erectile dysfunction is of particular concern after RARP, with prevalence varying from 14% to 90% [8].

Multiparametric MRI (mpMRI) is increasingly used to support the diagnosis, tumour localisation, and management of prostate cancer through three‐dimensional (3D) T2‐weighted imaging, diffusion‐weighted imaging with apparent diffusion coefficient, and dynamic contrast‐enhanced sequences [9]. mpMRI is also used by surgeons for surgical planning since a good understanding of the anatomy is essential to reduce the risk of complications. However, surgeons are expected to mentally reconstruct conventional two‐dimensional (2D) mpMRI into a 3D representation that matches the anatomy as seen through an endoscope during RARP [10]. Precise knowledge of the 3D location of the tumour and its relationship to the prostate capsule and neurovascular bundles (NVBs) can inform the surgical management and nerve‐sparing technique, whilst reducing PSMs [11, 12]. Although studies have shown that mpMRI induces surgeons to change their surgical plan, reducing PSMs [13], it is difficult for surgeons to imagine intra‐operatively the precise location of tumours entirely from preoperative multiparametric medical images, a process that becomes less challenging with experience.

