Some methods have been proposed to support the understanding of a patient's anatomy during surgery. 3D surgical navigation models have been displayed next to the surgeon console [12], overlaid on endoscopic videos using elastic‐based augmented reality [11], and made available to surgeons as 3D printed models during surgery [14]. Despite the variability reported in these studies, evidence from a recent literature review and meta‐analysis [15] suggests a trend towards a reduction in PSMs [11, 12, 14], with no clear evidence of the impact on functional postoperative outcomes. That review and meta‐analysis of the potential benefits of 3D models highlighted limitations in current studies, including a lack of comparison between 3D printed and virtual models, lack of description and justification for the methodology chosen, and studies contradicting each other. Moreover, the role of 3D virtual and 3D printed models in surgery is yet to be defined as there are many covariates that have an effect on outcomes, such as surgeon's expertise, location of cancer lesions, number of anatomical structures to be included, approaches for the creation of 3D models, among others.

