**Fig. 1 bju16850-fig-0001:**
[figure not shown]
Flow of participants and execution of our feasibility study. RARP, robot‐assisted radical prostatectomy.

The aim of this study is to measure the effect of 3D models on the reduction of PSM rates and on functional outcomes after RARP. Our main hypothesis is that there will be a reduction of positive resection margins (PSMs) and improvement of functional outcomes for patients undergoing RARP when surgeons are presented with a 3D printed or 3D virtual patient‐specific prostate model during surgery. Specifically, we hypothesise that 3D models reinforce the mental reconstruction of the anatomy that surgeons acquire via conventional 2D mpMRI whilst assisting surgeons in matching the precise location of the anatomy and lesions with respect to the endoscopic view they observe during RARP [10]. 3D models could inform the surgical management and nerve‐sparing technique, whilst avoiding increases in PSM rates. Studying both 3D virtual and 3D printed models will allow us to understand whether tactile information is important. We highlight the importance of recruiting surgeons across different levels of expertise to reduce bias and avoid having expertise as a confounder for the impact of 3D models on the reduction of PSMs. Therefore, we will stratify our results based on each surgeon's number of years of experience.

We will also report measures related to the deployment of this feasibility study in anticipation of a subsequent larger randomised controlled trial. Measures include patient recruitment rate, and percentage of cases that led to successful model deployment in the operating theatre.

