### Data Analysis

For analysis, we will report contingency tables, whereby the primary outcomes will be treated as categorical variables. We will use Pearson's chi‐squared probability distribution to compare the three groups (two interventional and one control), whereby both independent (treatment: 3D virtual or 3D printed models) and dependent (PSMs) variables are categorical. Our null hypothesis is that there is no difference among these three groups. We will conduct analysis at the significance level of *P* = 0.05. We will report mean, variability and CIs for the control group and intervention arms of PSMs and functional outcomes. When analysing continuous variables resulting from questionnaires related to functional outcomes, we will conduct parametric (one‐way anova) and non‐parametric (Kruskal–Wallis test) tests depending on the tests of normality, and run an ancova, while adjusting for multiple comparisons (e.g. Bonferroni) and including pairwise comparisons (independent *t*‐tests).

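### The primary margin comparison is an unadjusted chi-squared across non-randomised groups, although the protocol says outcomes depend on the surgeon and states nothing that balances surgeons over groups

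*Protocol article*

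**What the plan says.** **Analysis.** Data Analysis in the protocol article names a Pearson chi-squared "probability distribution to compare the three groups (two interventional and one control") for PSM, tested at 0.05. It continues: "We will report mean, variability and CIs for the control group and intervention arms of PSMs and functional outcomes". Questionnaire scores get one-way ANOVA or Kruskal-Wallis and an ANCOVA whose covariates are not named, "while adjusting for multiple comparisons (e.g. Bonferroni) and including pairwise comparisons" by independent t-tests. No surgeon term appears.

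**Surgeon effect.** The Background describes incontinence as "affected by surgical technique, surgeon's skill and patient characteristics" and says "there are many covariates that have an effect on outcomes, such as surgeon's expertise". Study Design adds "We highlight the importance of recruiting surgeons across different levels of expertise to reduce bias" and treats expertise as a potential confounder. Its remedy is to stratify results by years of experience, which Data Analysis does not take up.

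**Allocation.** Study Design says that the study is not randomised. Under Surface Model Generation, the choice between printed and virtual model follows resources and the days left before surgery. Under Control Group, prospective controls are to be propensity-matched on unnamed variables, and are included only if enough cases remain after the intervention arms are filled.

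**The concern.** Pearson's chi-squared treats all patients in a group as exchangeable with those in the other groups. If surgeons differ in PSM rate and one group holds more cases from surgeons with higher rates, the groups will differ without any effect of the models. The document names this mechanism itself, and its allocation rules leave the surgeon mix to circumstance.

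What is at stake is the primary comparison and, with it, the choice between printed and virtual models, which the Discussion says will inform a later randomised trial. A second, smaller matter is what the per-group confidence intervals describe: the PSM rate for the surgeons who took part, or for surgeons in general.

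**Working it through.** **Inputs from the article.** Groups of 54 printed, 54 virtual and 108 prospective controls; control PSM about 20% (Sample Size Determination). The article does not say which control group enters the three-group test; the prospective one is assumed here.

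**Inputs assumed.** The number of surgeons and the spread between them are not given. I take 4-8 surgeons and a between-surgeon log-odds SD of 0.3-0.5. At a mean of 20%, this puts the 10th to 90th centile of surgeon PSM rates at 14-26% (SD 0.3) to 11-31% (SD 0.5), an intraclass correlation (ICC) of about 0.014-0.038.

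**Step 1: the plan's own figure.** With effect 0.25, SD 0.5, power 0.75 and a one-sided Dunnett critical value of 1.916 (equal groups), n = 2 × 0.5² × (1.916 + 0.674)² / 0.25² = 53.7, so 54 per arm. With a 2:1 control and power 0.75 to detect both arms, the result is 107.2 and 53.6, so 108/54/54; adding 54 retrospective controls gives 270. The figures reproduce, and contain no allowance for surgeons.

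**Step 2: when the between-group test goes wrong.** Let w₁ⱼ and w₂ⱼ be surgeon j's share of the cases in two groups. Relative to the variance that the naive test assumes, the true variance of the difference is

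ratio = (1 − ICC) + ICC × Σ(w₁ⱼ − w₂ⱼ)² / (1/n₁ + 1/n₂).

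- Equal mix: the sum is 0 and the ratio is 1 − ICC, so the naive test is slightly conservative.
- For 54 against 108, 1/54 + 1/108 = 1/36. The ratio exceeds 1 once Σ(w₁ⱼ − w₂ⱼ)² > 1/36 = 0.028. With 6 surgeons this is a typical share difference of √(0.028/6) = 0.068, about 7 percentage points per surgeon. Random allocation from equal shares would give an expected sum of (1 − 1/6)/36 = 0.023, so harm begins at little more than chance imbalance.
- Extreme case, six different surgeons in each of the two groups: the sum is 1/6 + 1/6 = 1/3 and the ratio is 1 + 11 × ICC, or 1.22 at ICC 0.02 and 1.55 at 0.05.

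**Step 3: size for the three-group chi-squared at nominal 5%, by simulation with no treatment effect.**

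| Surgeon mix over groups | Pearson chi-squared | Cochran-Mantel-Haenszel by surgeon |
|---|---|---|
| Equal | about 5% | 4.4-5.6% |
| Moderately uneven | 5-7% | 4.4-5.6% |
| Strongly uneven | 6-11% | 4.4-5.6% |

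The last column is one range for all three mixes. Drawing each group's surgeon shares from a symmetric Dirichlet distribution with parameter 5 (moderate) or 1 (strong) reproduces these ranges. A separate beta-binomial simulation with 6 surgeons, ICC 0.02 and 0.05, and Dirichlet parameter 2 gives 6.4% and 8.6% for uneven mix, against 4.8% and 4.1% for balanced mix.

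**Step 4: the per-group intervals.** The naive 95% half-width at 20% is 1.96 × √(0.16/n): 10.7 points for n = 54 and 7.5 for n = 108.

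- For the participating surgeons with their actual case mix, a Wilson interval from 108 controls covers 95-96% (simulated with equal mix). Nothing is wrong.
- For a wider population of surgeons, the design effect is 1 + (m − 1) × ICC, with m patients per surgeon. With 6 surgeons and n = 108, m = 18. The design effect is 1.34 at ICC 0.02 and 1.85 at 0.05, and the half-width becomes 7.5 × √1.34 = 8.7 and, with unrounded inputs, 10.3 points. Coverage of the naive interval for that target is about 83-92% over the assumed range with equal mix.

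**The case against.** **Experience strata.** The plan to stratify by years of experience addresses the same mechanism, and should absorb whatever part of the surgeon effect experience explains. That stands. But surgeons of equal experience can differ, and the strata do not enter the named tests.

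**Other routes to balance.** Propensity matching, and the covariate-based replacement of patients who withdraw, might include the surgeon, and the ANCOVA might adjust for it. The variables are not named, so this cannot be excluded. Matching concerns controls against intervention arms and does not cover printed against virtual. The ANCOVA concerns questionnaire scores, not PSM.

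**A condensed article.** Covariate lists are commonly left to a fuller plan, which is not shown. This is fair for the ANCOVA. For PSM, however, the article fixes a specific unadjusted test, and a fuller plan would have to depart from it.

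**Uneven mix is not shown.** Allocation depends on timing and resources, not on surgeon, so the mix could turn out balanced. This stands, and makes the inflation conditional.

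**A stronger reading.** A reader might infer that all tests and intervals are too narrow, and that these intervals will be carried into the randomised trial. The documents do not support it. With equal mix the test is at or slightly below 5%, and the per-group intervals are right for the participating surgeons. What the article says it will take forward is the recruitment rate and deployment percentage (Study Design) and the choice of model (Discussion), not a PSM interval or an ICC. Nor could this study supply a usable ICC: with 4-8 surgeons and 216 patients, the simulated estimate was zero or negative in 35-36% of runs at SD 0.3 and 16-20% at SD 0.5.

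**Conclusion.** The point holds for the primary comparison. An unadjusted chi-squared is fixed for non-randomised groups, the document itself says that outcomes depend on the surgeon, and its only stated provision is partial and stays outside the tests. The consequence is conditional and moderate: a type I error of about 5-7% or 6-11% in place of 5% if the mix is moderately or strongly uneven, and no inflation if it is equal. These figures rest on the assumed 4-8 surgeons and log-odds SD of 0.3-0.5; the documents fix neither these nor the actual mix. The per-group intervals need a statement of what they describe, not a new method.

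**What to change.** In Data Analysis:

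1. Make the PSM comparison a Cochran-Mantel-Haenszel test stratified by operating surgeon, or a logistic regression with surgeon as a factor. Pool low-volume surgeons by a rule set in advance.
2. Include surgeon in the ANCOVA for functional scores.
3. Report the number of patients per surgeon in each group, so that the reader can see the mix.
4. State that the per-group confidence intervals apply to the participating surgeons and are too narrow if read as applying to surgeons in general.
5. If an ICC is reported, label it descriptive and give its uncertainty.

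The experience strata already require the operating surgeon to be known, so no further data or patients are needed. The cost is slightly less precision and sparse strata: a surgeon whose cases all fall in one group contributes nothing to the stratified test.

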### Endpoints

The primary study outcome is PSM rates measured after specimen analysis. Secondary outcomes include incontinence rates (pad weights, electronic Patient‐Reported Outcome Measures), erectile dysfunction (International Index of Erectile Function score, and Erectile Hardness Score), and International Consultation on Incontinence Questionnaire‐Urinary Incontinence (ICIQ‐UI) score captured at 3 months after surgery. Other secondary outcomes are related to our pipeline deployment metrics, including patient recruitment rate and percentage of cases that led to successful model deployment in the theatre.

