## Methods

### Interventions

Patients diagnosed with prostate cancer will undergo discussion at the weekly multidisciplinary team meeting at Guy's Hospital (London, UK) to decide management options. These patients will then be followed up in the clinic to determine those who opted for RARP. A list of those scheduled for RARP in the upcoming months will be collected. Patients will fill out questionnaires in the clinic regarding baseline functional information preoperatively related to potency and continence and these data will be stored on REDCap (Research Electronic Data Capture software). The hospital electronic health record will be used to collect data on patient demographics, staging, Gleason score, prior treatment for prostate cancer, potency and incontinence to eliminate patients not meeting our inclusion criteria.

Patients will then be contacted via telephone and informed about the study. They will be given written information via e‐mail or in person preoperatively on: (i) the aims of the study; (ii) the patient information materials available; and (iii) contact details of chief investigator.

Patients can consent verbally to participate in the study via telephone but can opt to withdraw any time before the surgery. They will then be given a written consent form to sign before their surgery, which will include permission to use their data. Pseudo‐anonymisation will be carried out by a Clinical Research Fellow to allow data processing and analysis by Data Scientists.

Once patients have consented verbally, mpMRI will be obtained and anonymised for extraction of anatomical structures. Histology data will also be collected from previous prostate biopsy to help better identify the exact location and size of lesions. These will then be reviewed by the radiologist to guarantee the patient is eligible given our inclusion criteria.

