### Methods of Data Collection

This will be a single‐centre study performed in the Urology Department of Guy's Hospital, London, UK. Specimen analysis will be carried out on the whole prostate gland removed from the patient during RARP to evaluate margin status and estimate PSMs. There will be no deviation from normal clinical practice.

At the 6‐week follow‐up, the surgeon will meet with the patient to present PSM status and capture functional outcomes from the patient via questionnaires. We will capture these measures as endpoints for analysis. These questionnaires will be re‐administered at 3, 6 and 12 months postoperatively.

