## Discussion

The identification of number and size of prostate cancer lesions prior to RARP has been limited to the 2D view of mpMRI scans and biopsy results. Surgeons are expected to mentally construct and visualise the exact location and dimensions of the lesions in 3D format prior to surgery [10]. The aim of prostate cancer surgery is to preserve maximum nerve function whilst preventing PSMs in order to achieve good functional outcomes. To accomplish this, a better understanding of prostate cancer lesions and the surrounding anatomy is needed [14]. 3D modelling has the potential to enhance surgical planning by providing surgeons with an intra‐operative navigation tool to better appreciate the nature of lesions [11].

A few studies have been conducted using either 3D virtual models or 3D printed models for RARP. Despite varying results, a number have shown a decrease in PSM rates irrespective of the model used; however, only one showed a statistically significant improvement [15]. That study, by Checcucci et al. [20], involved a total of 800 patients, with 3D virtual models created for 640 of these patients. The authors showed a PSM rate of 25% in the 3D virtual model group vs 33% in the control group [20]. To date, most studies have not used inclusion criteria that involve type of lesion, location of lesion, tumour stage or Gleason score [10, 11, 20, 21, 22, 23]. Because a lesion location that is close to the capsule or NVBs can make a significant difference to how conservatively the surgeon approaches the NVBs and the likelihood of PSMs, we have decided to exclude anterior lesions and lesions located far from the capsule to assess the true impact of the models. In addition, most studies have looked at either 3D virtual or 3D printed models [15]. In order for us to assess which is more effective in a similar cohort of patients at a single centre, we have chosen to compare both. This will help us further decide which type of model to use for a randomised controlled trial in the future.

Despite evidence showing a reduction of PSMs, comparatively few data are available showing the impact of 3D prostate models on functional outcomes, with a recent meta‐analysis showing no clear difference in postoperative and functional outcomes in the intervention groups [15]. For this reason, we will follow up patients at regular intervals for up to a year to assess the effects on incontinence and potency.

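### Functional outcomes: the endpoint time is 6 weeks in one place and 3 months in another, and a normality-selected test, an ANCOVA and covariate-free t-tests are all planned with no main analysis named

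*Protocol article*

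**What the plan says.** **Timing.** The Endpoints section lists the functional secondary outcomes and ends the list with the ICIQ-UI "score captured at 3 months after surgery". The grammar leaves open whether 3 months covers the whole list or only that score. Methods of Data Collection says that at the 6-week visit "the surgeon will meet with the patient to present PSM status and capture functional outcomes from the patient via questionnaires", and continues: "We will capture these measures as endpoints for analysis". The Abstract says the same. The questionnaires are then to be "administered at 3, 6 and 12 months postoperatively". The Discussion adds that "we will follow up patients at regular intervals for up to a year to assess the effects on incontinence and potency".

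**Analysis.** For continuous questionnaire variables, the Data Analysis section chooses between one-way ANOVA and Kruskal–Wallis, with "tests depending on the tests of normality, and run an ancova". The same sentence provides for a multiplicity adjustment (Bonferroni is the example) and gives independent t-tests as the pairwise method. It does not say which result is the main one.

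**Context.** The Study Design section states that the study is not randomised, and it names surgeon expertise as a possible confounder. Under Surface Model Generation, the intervention arm depends on production resources and the days left before surgery. Baseline function is collected: "Patients will fill out questionnaires in the clinic regarding baseline functional information preoperatively related to potency and continence".

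**The concern.** Better functional outcome is part of the main hypothesis in the Study Design section, and the Discussion presents it as the gap in current evidence. A reader of the final report needs to know which visit and which analysis give the answer for each instrument. The text gives two candidate times and several candidate analyses.

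The analyses can disagree for a substantive reason. Groups are not formed by chance, so a comparison with no covariates and one adjusted for baseline estimate the effect under different assumptions. If they differ, nothing in the text says which counts.

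The pairwise step has its own inconsistency. A failed normality check changes the overall test, but the stated pairwise method remains the t-test.

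**Working it through.** **1. Times set side by side**

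| Section | Time | Status given |
|---|---|---|
| Endpoints | 3 months | Secondary outcome time, at least for ICIQ-UI |
| Abstract; Methods of Data Collection | 6 weeks | Measures captured then are called endpoints for analysis |
| Abstract; Methods of Data Collection | 3, 6 and 12 months | Questionnaires repeated |
| Discussion | Up to 1 year | Follow-up period; no endpoint time named |

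The first two rows conflict. The last two assign no role to the 6- and 12-month visits.

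**2. Planned analyses set side by side**

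| Analysis | Condition | Covariates | Multiplicity correction over pairs |
|---|---|---|---|
| One-way ANOVA | Normality not rejected | None | Not applicable |
| Kruskal–Wallis | Normality rejected | None | Not applicable |
| ANCOVA | None stated | Yes (not listed) | Not applicable to the overall test |
| Independent t-tests | None stated | None | Yes |

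Each score therefore has an overall test without covariates, an adjusted overall test and a set of covariate-free pairwise tests.

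**3. Group sizes for the illustration.** The plan states no figure for the functional outcomes. The three-group sizes 54/54/108 come from Sample Size Determination and concern the primary outcome. They reproduce with a one-sided Dunnett test at 0.05, effect 0.25, SD 0.5 and a 2:1 control: the critical value is 1.936 and the power to detect both arms is 0.754, against the stated 0.75. The present point does not rest on this.

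**4. Null simulation for one outcome.** These settings are assumptions, not taken from the documents:
- baseline and four visits, with equal correlation of 0.4, 0.6 or 0.8 between all times;
- normal or lognormal data, so six scenarios of 3,000 runs each;
- no true group difference and no confounding;
- Shapiro–Wilk at 0.05 on pooled residuals to choose ANOVA or Kruskal–Wallis;
- ANCOVA on baseline (F test on 2 and 216 − 4 = 212 degrees of freedom);
- Bonferroni as min(1, 3 × smallest of the three t-test p-values).

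| Rule for declaring a result at 5% | False-positive rate, range over scenarios |
|---|---|
| One ANCOVA, one fixed time | 0.043–0.051 |
| Overall test selected by the pre-test, one time | 0.045–0.051 |
| Any pairwise t-test with Bonferroni, one time | 0.039–0.045 |
| Any pairwise t-test without Bonferroni, one time | 0.114–0.128 |
| Any of selected overall test, ANCOVA or Bonferroni t-tests, one time | 0.073–0.105 |
| ANCOVA at any of four times | 0.156–0.184 |
| Any of the three analyses at any of four times | 0.235–0.279 |

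The independence value for one test at four times is 1 − 0.95⁴ = 0.185, which agrees with the ANCOVA row. Monte Carlo standard errors are about √(0.05 × 0.95 / 3000) = 0.004 near 5% and √(0.25 × 0.75 / 3000) = 0.008 near 25%.

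The inflation comes from leaving the time and the analysis open. Neither the pre-test nor the corrected t-tests cause it alone. Because the simulation has no confounding, it does not measure the bias that covariate-free comparisons may carry here.

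**The case against.** The strongest defence has four parts.

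- **These are secondary outcomes in a feasibility study, and an SAP may name the main model and visit.** This stands as a limit on severity. But an SAP cannot follow both statements of the endpoint time, and the pre-test rule and the t-tests are already fixed in the text.
- **The timing conflict may be milder than it looks.** The sentence after the 6-week visit could describe which measures are captured rather than when, and 3 months may apply only to the ICIQ-UI. Both readings are possible. Even so, the ICIQ-UI is a questionnaire score with two candidate times, and the wording needs to be aligned.
- **Propensity-score matching already deals with group differences.** The Control Group section plans 1:2 matching of controls to the intervention arms. That helps for those comparisons, but it does not address printed against virtual models, and prospective controls are included only if enough cases remain.
- **The pre-test does no harm to type I error.** The simulation supports this (0.045–0.051).

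A reader might also infer several stronger points that the documents do not support:

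- That the t-tests are uncorrected for multiplicity. The sentence that plans them provides for a correction. They lack only covariates.
- That choosing Kruskal–Wallis removes baseline adjustment. The ANCOVA is an addition and is not conditional on normality.
- That 12 months is a third declared endpoint. It is a follow-up time with no assigned role.
- That five measures at four visits give 20 results and a false-positive chance of 1 − 0.95²⁰ = 0.64. This treats repeated and overlapping scores in the same men as independent. It also assumes a visit schedule for pad weights that is not given, and that the multiplicity correction applies only within each result.

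**Conclusion.** The point holds in two parts. First, 6 weeks and 3 months conflict as the functional endpoint time, at least for the ICIQ-UI, and the 6- and 12-month visits have no stated role. Second, the plan sets a normality-selected overall test, an ANCOVA and covariate-free t-tests side by side without naming a main analysis, and its pairwise method does not change when normality is rejected.

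If any planned result may be quoted, the illustrative false-positive rate per outcome is about 7–11% at one time and 24–28% over four times, against about 5% for a single ANCOVA at a fixed time. These figures depend on the assumed correlations and distributions and on free choice among results. They show what the text leaves open and do not predict what the investigators will do. The possible disagreement between adjusted and unadjusted answers follows from the non-randomised design and is not quantified here. The plan should be changed on this point, but the primary outcome is not affected.

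**What to change.** 1. Delete the normality pre-test. For each instrument, make one baseline-adjusted model the main analysis: either the ANCOVA already planned or a repeated-measures model over the visits. Include the preoperative score and pre-specified confounders such as surgeon experience, and use robust standard errors.
2. Take pairwise contrasts from that model, with the multiplicity adjustment already foreseen, in place of independent t-tests. Any rank-based analysis should be labelled as sensitivity analysis.
3. Reconcile the Abstract, Endpoints and Methods of Data Collection to one key functional time chosen by the sponsor. State whether it applies to every functional outcome, and label the other visits supportive.

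**Cost.** Wording and minor extra analysis work; no added visits or patients. Men without a preoperative questionnaire, possibly including retrospective controls, cannot enter a baseline-adjusted model directly, so a separate rule is needed for them.
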